### Inclusion and exclusion criteria

One hundred and twenty-four CAD patients undergoing PCI with LVH (LVMI > 120 and 100 g/m^2^ for men and women, respectively) at Sir Run Run Shaw Hospital of Zhejiang University will be enrolled in the trial. The enrollment period is expected to be finished in 2020. Detailed inclusion and exclusion criteria are listed in Table 2. The attending physician is responsible for the inclusion of patients. Patients treated with other medications which would affect cardiac metabolism, and patients who are concomitant with other causes of myocardial ischemia or other causes of LVH will be excluded from the study.

**Table 2 Tab2:** Inclusion and exclusion criteria

**Inclusion Criteria**	
● CAD patients with hypertensive LVH who receive PCI.	
● Male and female aged 18–70 years.	
● Coronary stenosis is greater than 70% before PCI performed, and < 20% after PCI, with no need for other angioplasty.	
● Trimetazidine naive.	
● Provided informed consent.	
**Exclusion Criteria**	
● Utilization of trimetazidine, coenzyme Q10 or other medications which would affect cardiac metabolism.	
● Concomitant with other causes for left ventricular hypertrophy, such as aortic constriction, hypertrophic cardiomyopathy and cardiac valvular disease.	
● Concomitant with other causes for myocardial ischemia, such as congenital heart disease, rheumatic heart disease, dilated cardiomyopathy.	
● Presentation with an acute myocardial infarction.	
● Severe liver and kidney dysfunction (hepatic transaminase levels > 3 x ULN, bilirubin > 1.5 x ULN, eGFR < 30 mL/min/1.73m^2^).	
● Heart function defined as New York Heart Association IV, or LVEF < 30%.	
● Pregnancy or lactating, or possibility of a future pregnancy.	
● History of cancer.	
● Life expectancy less than 12 months.	

*CAD* coronary artery disease, *LVH* left ventricular hypertrophy, *PCI* percutaneous coronary intervention *ULN* upper limit of normal range, *eGFR* estimated glomerular filtration rate, *LVEF* left ventricular ejection fraction

### Exclusion criteria during the follow-up periods

Every participant will have the right to withdraw from the study without restriction, and participants may be removed if
Patients’ demand to withdraw the informed consent.Study protocol violation (including poor compliance).Lost to follow-up.Pregnancy or new-onset malignant tumor during the follow-up.Detrimental to the patient’s well-being.

Every withdrawal will be recorded in the CRFs, and a visit will be arranged if possible.

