## Methods/design

### Study design

It is the first prospective, placebo-controlled study to explore the relationship between trimetazidine and ventricular remodeling. CAD patients undergoing PCI with LVH will be randomized to receive trimetazidine (35 mg twice a day) or placebo for 12 months after PCI. Coronary intervention and other medication therapy will be performed according to current guidelines, and no difference in the use of angiotensin-converting enzyme inhibitor (ACEI), angiotensin receptor blocker (ARB) and aldosterone antagonist should be ensured between the two groups. The web-based randomization will be used for a 1:1 ratio grouping to either trimetazidine or placebo. Secretary of department of cardiology accesses the website via account password and is responsible for randomization. Block randomization will be stratified by concomitant medications (ACEI, ARB or aldosterone antagonist), sex and family history and it is blind to those who enroll participants or assign interventions. Blood biochemistry, echocardiography, Seattle Angina Questionnaire, 6-min walk test (6-MWT), exercise electrocardiography test and MACEs will be collected at the 3- and 12-smonth clinical follow-ups. All personal information will be converted to the new subject number. The attending physicians are responsible for data entry. Data monitoring committee is responsible for data security and accuracy. Committee members ([name], [name] and [name]) have access to the final dataset and periodically range check for data values.

The primary end point is the change of ventricular remodeling assessed by left ventricular mass index (LVMI) at 3- and 12-month follow-up after PCI compared with the baseline. The secondary end points will be the symptom of angina assessed by Seattle Angina Questionnaire, myocardial ischemia measured by 6-MWT and exercise electrocardiography test, as well as MACEs (defined as a composite of death, myocardial infarction, stroke, recurrent angina, re-hospitalization, change of viable myocardium). Details of the proposed study, including enrollment and follow-up visits, are outlined in Table 1. All serious adverse events must be reported to the sponsor immediately or within 24 h in case report forms (CRFs).

**Table 1 Tab1:** Study plan

Activity	Visit 0 screening	Visit 1	Visit 2
	0 day	3 months ±7 day	12 months ±7 day
Inclusion/exclusion criteria	×		
Informed consent	×		
Randomization	×		
Demography and medical history	×		

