#### Analysis

The final results will be presented on an intention-to-treat (ITT) basis. All data will be presented as percentages or mean ± standard deviation (SD). The comparison of data will be performed using the Chi-squared test (categorical variables) or Student’s t test (continuous variables). Cumulative incidences of end points in 12 months after PCI will be calculated using Kaplan-Meier methods. Log-rank tests will be used for comparisons between groups. Possible covariables will be incorporated in the analysis if certain important baseline levels are still not matched after randomization. Mean imputation will be used to handle missing data. A *p*-value < 0.05 will be considered significant. All statistical analyses will be performed using the Statistical Package for Social Sciences (SPSS), version 20.0 (SPSS Inc., Chicago, IL, USA). The results will be published by chief investigator and major contributors.

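### Removal from the study for poor compliance or protocol violation sits badly with the ITT analysis, because the outcomes of removed patients are not secured

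*Protocol article*

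**What the plan says.** The section Exclusion criteria during the follow-up periods applies after randomisation. It first gives every participant the right to withdraw, then says "participants may be removed if" one of several conditions is met. Besides withdrawal of consent and loss to follow-up, these are "Study protocol violation (including poor compliance", "Pregnancy or new-onset malignant tumor during the follow-up" and "Detrimental to the patient’s well-being". On what happens next it says: "Every withdrawal will be recorded in the CRFs, and a visit will be arranged if possible". It does not mention stopping study drug as something distinct from leaving the study.

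The Analysis section says "The final results will be presented on an intention-to-treat (ITT) basis" and "Mean imputation will be used to handle missing data".

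Under Study design, the primary end point is the change in ventricular remodeling assessed by "left ventricular mass index (LVMI) at 3- and 12-month follow-up after PCI compared with the baseline". MACEs are collected at the same two visits. Study procedures adds that adherence is monitored, for example by tablet return.

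**The concern.** An intention-to-treat comparison needs the outcomes of all randomised patients, including those who take little study drug or depart from the protocol. Listing poor compliance as a reason to remove someone from the study works against that. A patient removed at month 4, say, has no assured 12-month echocardiogram and no assured record of later MACEs.

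Compliance and well-being can depend on tolerability or on lack of benefit, so the patients removed may differ between arms in number and in prognosis. The patients with observed outcomes would then no longer be comparable in the way randomisation made them. Mean imputation does not restore this, because it takes no account of why a value is missing. An analysis plan written later cannot recover outcomes that were never collected, so the protection has to be in the protocol.

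**Working it through.** **The plan's own figures.** Sample size gives 70% versus 40% response, 90% power, 0.05 significance, 56 per group and 124 in total with 10% non-assessable. Two-sided, without continuity correction, with mean rate 0.55:

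n = [1.960·√(2·0.55·0.45) + 1.282·√(0.21 + 0.24)]² / 0.30² = (1.379 + 0.860)² / 0.09 ≈ 55.7, so 56 per arm.

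This reproduces the stated number, and 112 × 1.10 = 123.2 gives 124. With 62 randomised per arm and 10% lost, 55.8 per arm remain and power is 90.1%; at 20% lost it is 86.3%. Loss of precision is therefore modest. The issue is bias.

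**Bias on the LVMI scale.** All removal inputs are assumed; the documents give none by arm. Let r₁ and r₂ be the shares removed and δ the amount, in SD of LVMI change, by which removed patients do worse than those retained. With no true effect and analysis of observed cases:

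- bias b = (r₁ − r₂)·δ, in favour of the arm with more removed
- SE = √[1/(62(1 − r₁)) + 1/(62(1 − r₂))]
- type I error ≈ Φ(−1.96 + b/SE) + Φ(−1.96 − b/SE)

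| Removed, arm 1 / arm 2 | δ | b (SD) | SE | b/SE | Type I error |
|---|---|---|---|---|---|
| 10% / 10% | 1.0 | 0 | 0.189 | 0 | 5.0% |
| 10% / 5% | 0.5 | 0.025 | 0.187 | 0.13 | 5.2% |
| 10% / 5% | 1.0 | 0.050 | 0.187 | 0.27 | 5.8% |
| 10% / 0% | 0.5 | 0.050 | 0.185 | 0.27 | 5.8% |
| 10% / 0% | 1.0 | 0.100 | 0.185 | 0.54 | 8.4% |
| 15% / 0% | 1.0 | 0.150 | 0.187 | 0.80 | 12.6% |

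Simulation of the same scenarios agrees: about 5.0 to 5.7% for 10% versus 5%, and about 5.9 to 12.3% when only one arm loses patients.

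**Bias on the response scale**, which the sample size uses. Assume a true response of 40% in both arms, 10% of placebo patients removed at random, and 10% of trimetazidine patients removed whose response rate is q. The observed trimetazidine rate is (0.40 − 0.10q)/0.90: 44.4% for q = 0 and 42.2% for q = 0.20. The spurious difference is 2.2 to 4.4 percentage points and type I error 5.7 to 7.6%. So equal shares alone do not guarantee safety; prognosis of the removed must be alike too.

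**What belongs to imputation instead.** If 10% in each arm are replaced by their arm mean, the naive SE is about 0.9 of the true one, and type I error is about 2Φ(−1.96 × 0.9) = 7.8% with no bias at all. That inflation comes from the imputation method, so it is kept out of the table.

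**The case against.** A reader might infer that the two sections flatly contradict each other: that removed patients are dropped from the analysis, that all their data collection ends, and that the resulting gaps are related to treatment. The text supports none of these outright. The wording is permissive, it does not say who decides, and nothing says that removed patients leave the analysis set. A patient no longer followed can still be counted in the randomised arm with an imputed value. A further visit is foreseen, and the section neither promises nor rules out further collection. Treatment-related missingness is a reasoned risk and not a documented fact. The trial is placebo-controlled, with allocation concealed from those who enrol or assign, which limits discretionary removal by arm, though not removal driven by tolerability. Nurses support attendance.

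It can also be said that a condensed article leaves discontinuation procedures and the definition of the ITT set to the full protocol or SAP. That does not answer the point. The article states a rule, under a heading about exclusion, that names poor compliance as a ground for leaving the study. The rule is what conflicts in principle with intention to treat, and an optional visit does not secure the scheduled 3- and 12-month assessments.

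The objection to size also stands in part: removal in one arm only is a worst case, and the same rule applies to both arms.

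**Conclusion.** The point holds as a tension between a stated removal rule and a stated analysis principle, with a conditional risk of bias. It is not a proven exclusion of patients from the ITT set. If removal differs by arm and relates to prognosis, plausible moderate imbalance (10% versus 5%, removed patients 0.5 to 1.0 SD worse) gives about 0.02 to 0.05 SD of bias and a type I error barely above nominal. The worst case considered gives 0.15 SD and about 12%. There is no bias if removal is balanced in both share and prognosis. Every one of these sizes rests on assumed removal shares and prognosis. The 10% planned as non-assessable shows only that missing outcomes on this scale are expected overall, not that they will be unequal between arms. Withdrawal of consent and loss to follow-up are unavoidable and are not criticised.

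**What to change.** Reconcile Exclusion criteria during the follow-up periods with Analysis:

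- Separate stopping study drug from leaving the study.
- Delete poor compliance and protocol violation as grounds for removal from the study.
- Keep all randomised patients, including those who stop study drug for any reason, in the scheduled 3- and 12-month echocardiography, questionnaire and MACE follow-up, unless they withdraw consent to data collection.
- Analyse them in their randomised arm, with any per-protocol analysis as secondary only.

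When study drug should be stopped is a clinical matter and is not prescribed here. The cost is a change of wording and a few already scheduled visits for patients who are off study drug.

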### Study procedures

The study protocol is shown in Fig. 1 and Table 1. Patients are randomly allocated to receive trimetazidine (35 mg twice a day) or placebo for 12 months after PCI. All interventions are performed strictly comply with the standard. Physical examination, blood test, 12-lead electrocardiogram, echocardiography, symptoms of angina, 6-MWT, exercise electrocardiography test and quality of life will be collected at baseline visit and every follow-up visit. Blood tests will include complete blood count (CBC), alanine aminotransferase (ALT), aspartate aminotransferase (AST), serum creatinine (Scr), blood ureanitrogen (BUN), low-density lipoprotein cholesterol (LDL-C) and N-terminal pro-B–type natriuretic peptide (NT-proBNP). MACEs will be collected at 3- and 12-month follow-up. Research nurses will inform patients of the follow-up time in advance. They are helpful for completion of follow-up and monitoring adherence (e. g, drug tablet return).

**Fig. 1 Fig1:**
[figure not shown]
Flow chart

### Primary end point

The primary end point in this study is the change between baseline and follow-up LVMI (calculated as the ratio: left ventricular mass (LVM)/ body surface area). Two-dimensional and Doppler echocardiography will be performed to quantify left ventricular function and structure (Phillips Healthcare) [21]. Ventricular remodeling will be assessed by calculating LVMI using Devereux formula. Interventricular septum thickness (IVST), left ventricular end-diastolic dimension (LVEDd), left ventricular posterior wall thickness (LVPWT) will be measured by echocardiography. LVM = 1.04[(IVST + LVEDd + LVPWT)^3^-LVEDd^3^]-13.6 g.

### Secondary end points

The secondary end points are the change the symptom of angina and myocardial ischemia, and the 3- and 12-month incidence of MACEs. The symptom of angina will be assessed at baseline, 3- and 12-month follow-up period by Seattle Angina Questionnaire. The improvement of myocardial ischemia and exercise capacity will be measured using exercise electrocardiography test and 6-MWT. The 6-MWT is a sample, low-cost method for estimating exercise capacity and will be performed according to standard procedures [22]. Clinical characteristics and a multipurpose health survey that consists of 36 questions (short form-36, SF-36) will be recorded at baseline, 3 months and 12 months. MACEs are defined as a composite end point of death, myocardial infarction, stroke, recurrent angina, re-hospitalization, change of viable myocardium.

### Trial committees

[name] guides the research team and provides overall supervision for the trial. The data monitoring committee ([name], [name] and [name]) is responsible for reviewing and monitoring data safety. Investigators have the right to reveal a participant’s allocated intervention or terminate the study in advance after discussion with [name] in the event of safety issues during the study as well as notify the ethics committee.

### Statistical considerations

#### Sample size

According to previous study [20], we hypothesized trimetazidine group has an effective rate of 70% to improve the left ventricular remodeling by reducing LVMI and placebo group has 40%, thus 56 patients in each group are necessary to offer 90% power at 0.05 significant level according to 1:1 ratio of random grouping. Anticipating 10% of patients potentially non-assessable according to previous experience on 12-month study, 124 randomized patients in total are needed.

#### Analysis

The final results will be presented on an intention-to-treat (ITT) basis. All data will be presented as percentages or mean ± standard deviation (SD). The comparison of data will be performed using the Chi-squared test (categorical variables) or Student’s t test (continuous variables). Cumulative incidences of end points in 12 months after PCI will be calculated using Kaplan-Meier methods. Log-rank tests will be used for comparisons between groups. Possible covariables will be incorporated in the analysis if certain important baseline levels are still not matched after randomization. Mean imputation will be used to handle missing data. A *p*-value < 0.05 will be considered significant. All statistical analyses will be performed using the Statistical Package for Social Sciences (SPSS), version 20.0 (SPSS Inc., Chicago, IL, USA). The results will be published by chief investigator and major contributors.

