There were also studies in recent years exploring possible molecular mechanisms. The rat model of aortic constriction was established to induce myocardial metabolic disorder within 7 days, and it was found that trimetazidine pretreatment could improve the myocardial energy metabolism by reducing serum levels of oxidative stress markers, attenuating the induction of genes related to myocardial hypertrophy, inhibiting the up-regulation of serum neuropeptide Y (NPY) levels, and further increasing the expression of myocardial NPY receptors [27]. This not only demonstrated that trimetazidine pretreatment could reverse acute metabolic disorders, but also revealed the underlying pathophysiological process of metabolic remodeling before the onset of myocardial remodeling.

Other researchers verified in vivo and in vitro that trimetazidine could effectively inhibit myocardial fibrosis through nicotinamide adenine dinucleotide phosphate (NADPH) oxidase-reactive oxygen species (ROS)-connective tissue growth factor (CTGF) signaling pathway [28]. However, those results were obtained just from animals and need to be supported by clinical trials.

In our study, stratified randomization will be used to reduce the possibility of variable imbalance. Thus, no difference will exist in the use of ACEI, ARB and aldosterone antagonist between groups. Nonetheless, it is possible that some baseline levels are still not matched after randomization. In this case, we believe that it occurs “by chance” and is a small probability event. Those variables (*p* < 0.05) will be adjusted. But in addition to statistical considerations, we will also assess the relationship between the adjusted covariates and the end points, rather than unselectively adjust them.

This study has some limitations. First, though the proposed study is designed as a randomized, placebo-controlled study, it is a single-center study, which may cause the baseline drift of the selected patients. Second, the causes of LVH are various. Hypertension, obesity and other pathologic disorders can cause an increase in the hemodynamic burden and lead to LVH. Thus, the findings of this study may not be applied to LVH caused by all diseases.

In conclusion, this trial will first investigate trimetazidine treatment (35 mg twice a day for 12 months) on the ventricular remodeling in CAD patients with LVH. We expect that the study results will confirm whether trimetazidine treatment can significantly improve ventricular remodeling.

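### The default primary comparison is an unadjusted t test on change in LVMI; baseline LVMI and the stratification factors enter only if a baseline significance test triggers them

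*Protocol article*

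**What the plan says.** The Primary end point section defines a continuous outcome: "The primary end point in this study is the change between baseline and follow-up LVMI". The Study design section places it at two times, as "left ventricular mass index (LVMI) at 3- and 12-month follow-up after PCI compared with the baseline".

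The Analysis section names two tests for comparing the groups, chi-squared for categorical data and Student's "t test (continuous variables") for the rest. Its only provision for covariates is conditional: "Possible covariables will be incorporated in the analysis if certain important baseline levels are still not matched after randomization". The Discussion gives the trigger, "Those variables (*p* < 0.05) will be adjusted", and qualifies it: "we will also assess the relationship between the adjusted covariates and the end points, rather than unselectively adjust them".

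On allocation, the Study design section says "Block randomization will be stratified by concomitant medications (ACEI, ARB or aldosterone antagonist), sex and family history". No section carries these factors, or baseline LVMI, into the analysis by default.

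Entry requires hypertrophy defined as "LVMI > 120 and 100 g/m^2^ for men and women, respectively". Table 1 schedules echocardiography at the screening visit, which serves as the baseline.

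**The concern.** Three features of the plan together lose information that the trial will already hold.

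1. **Baseline LVMI.** A change score assumes that follow-up LVMI rises one for one with baseline. Patients are selected for a high value on the measurement that also serves as baseline, so regression to the mean makes a slope below 1 likely. The t test leaves the resulting variation in the error term.
2. **Stratification factors.** If drug use, sex or family history predict LVMI, balancing on them and then leaving them out of the analysis makes the standard error too large. Sex already has its own LVMI cut-off in the entry rule.
3. **The adjustment rule.** Covariates are chosen by baseline p-values and then by a judgement on their relation to the end points. The primary model is therefore unknown until data have been examined.

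At stake are precision in a trial of 124 patients and a primary model fixed in advance.

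**Working it through.** **The plan's own figure.** The Sample size section uses 70% against 40%, 90% power and alpha 0.05. The two-sided pooled formula gives n = [1.960·√(2·0.55·0.45) + 1.282·√(0.7·0.3 + 0.4·0.6)]² / 0.30² = 55.7, so 56 per group, as stated. Then 112 × 1.1 = 123.2, so 124 (dividing by 0.9 gives 125). The figure reproduces, but it is for a binary response rate. It contains no LVMI SD and no correlation, so it cannot calibrate the loss below.

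**Loss from not using baseline LVMI as a covariate.** Let β be the within-arm slope of follow-up on baseline. Then:

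change-score error variance = ANCOVA error variance + (1 − β)² × baseline variance.

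The second term is never negative. Apart from one degree of freedom, ANCOVA cannot be less precise, whatever the correlation.

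With equal SDs at baseline and follow-up, β = r and the variance ratio is 2(1 − r)/(1 − r²) = 2/(1 + r). The article does not give r, so the values here are assumptions:

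| Assumed r | 2/(1+r) | Extra patients needed by the t test |
|---|---|---|
| 0.3 | 1.538 | 54% |
| 0.5 | 1.333 | 33% |
| 0.7 | 1.176 | 18% |
| 0.9 | 1.053 | 5% |

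For a hypothetical mean effect with 90% power by the t test on change, ANCOVA at the same size would have about 94.0% (r = 0.7) to 96.3% (r = 0.5).

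**Effect of the entry cut-off.** Selecting on high baseline LVMI breaks the equal-SD assumption. Let t be the fraction of baseline variance that remains after selection, and r the correlation before selection. The penalty becomes t(1 − r)/(1 + r). For a normal variable cut at its mean, t is about 0.36:

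- r = 0.5: 0.36 × 0.5/1.5 = 12%
- r = 0.7: 0.36 × 0.3/1.7 = 6%

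The position of the cut is illustrative, since the article does not describe the LVMI distribution.

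**Does the conditional rule make up for this?** Under randomisation a given baseline variable reaches p < 0.05 about one time in twenty, and stratification makes imbalance in the strata less likely still. The variables that belong in the model will therefore seldom be brought in. With 56 per arm, a baseline LVMI difference of up to about 1.98 × √(2/56) = 0.37 SD stays under the trigger. At an assumed slope of 0.5 to 0.7, that shifts the difference in mean change by (1 − 0.5) × 0.37 = 0.19 SD to (1 − 0.7) × 0.37 = 0.11 SD, uncorrected.

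**Stratification factors.** The article gives nothing on how strongly they predict LVMI, so this loss can be given a direction but not a size.

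**The case against.** The strongest reply is that a t test on change in a randomised trial is valid and unbiased over repeated randomisations. The plan does use baseline, by subtraction, and it does provide for imbalance. A condensed article may also leave model covariates to an analysis plan that is not shown. Most of this stands, and it makes the point one of efficiency and prespecification. The last part stands only partly, because the article itself names the test and fixes the rule for adjustment.

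The Sample size section is built on a response rate and the Analysis section also lists a chi-squared test. It could therefore be argued that the primary comparison is not settled as a t test. But both sections that define the end point describe a change in LVMI, which falls under the rule for continuous variables.

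A reader might infer stronger claims that the article does not support:

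- **That baseline LVMI is ignored.** It is subtracted; it is not used as a covariate.
- **That the analysis is unadjusted in all circumstances.** The Analysis and Discussion sections allow adjustment after an observed imbalance.
- **That the plan wastes a known 18% to 33% of patients.** That range is only r = 0.7 to 0.5 with equal SDs. It covers baseline LVMI alone, and selection at entry can bring it well below 18%.
- **That the trial's own power is wrong by the amounts shown.** The 56 per group was not sized on a mean change.
- **That omitting the strata invalidates the test.** If the strata are prognostic, the unadjusted standard error is conservative.

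**Conclusion.** The point holds as a recommendation that should be taken up. By default the primary comparison is a t test on change, with neither baseline LVMI nor the stratification factors as covariates, and the rule that could add them depends on the data. The direction of the loss does not depend on the correlation. Its size does: 54% to 5% more patients for an assumed r of 0.3 to 0.9 with equal SDs, and about 12% to 6% for r of 0.5 to 0.7 if entry truncates baseline LVMI at its mean. Omitting the strata adds an unquantified loss if they are prognostic. Confidence is high on the direction and the remedy, and low on the size.

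**What to change.** - Prespecify the primary analysis as ANCOVA of LVMI on arm, baseline LVMI and the randomisation factors (ACEI, ARB or aldosterone antagonist use; sex; family history). The month-12 contrast of a repeated-measures model with the same covariates is an alternative. Report the adjusted mean difference with its 95% CI.
- Delete the p < 0.05 imbalance trigger and the later selection of covariates by their relation to the end points.
- Use the same form, each with its own baseline, for the Seattle Angina Questionnaire, the 6-minute walk test and the SF-36.
- Keep the t test on change as a supportive analysis.
- If an efficiency gain is quoted, give it as 2/(1+r), with r and the equal-SD condition stated as assumptions.

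The cost is analysis wording only. LVMI is needed to enrol a patient and the strata to randomise one, and Table 1 already schedules baseline angina symptoms, walk test and quality of life.

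### Covariates enter the analysis only after a significant baseline test and an unspecified end-point check, so baseline LVMI is usually left out and the covariate set is not fixed in advance

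*Protocol article*

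**What the plan says.** The default comparison is unadjusted. Under Analysis: "The comparison of data will be performed using the Chi-squared test (categorical variables) or Student’s t test (continuous variables". Adjustment is conditional: "Possible covariables will be incorporated in the analysis if certain important baseline levels are still not matched after randomization". That section names no covariates and does not define a failure to match.

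The Discussion supplies the definition: "Those variables (*p* < 0.05) will be adjusted". It then adds a second condition: "we will also assess the relationship between the adjusted covariates and the end points, rather than unselectively adjust them". Of an imbalance that remains after randomisation, the authors write that "we believe that it occurs “by chance” and is a small probability event".

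Two other statements bear on the point. Under Primary end point: "The primary end point in this study is the change between baseline and follow-up LVMI". Under Study design: "Block randomization will be stratified by concomitant medications (ACEI, ARB or aldosterone antagonist), sex and family history". Neither baseline LVMI nor any stratification factor is named as a covariate.

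**The concern.** In a randomised trial, a baseline significance test asks whether a difference arose by chance. The authors already accept that it did. The test says nothing about whether the variable predicts the outcome, which is what makes adjustment worthwhile. A strong predictor is flagged about 5% of the time, and so is an irrelevant one.

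Three consequences follow:

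- Baseline LVMI, the obvious predictor of change in LVMI and measured in every patient at screening, is normally left out.
- Imbalances that matter but fall short of significance stay uncorrected.
- Which covariates enter is settled only after randomisation, partly by a check with no stated criteria.

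The stratification factors are the variables least likely to reach p < 0.05, because stratification balances them. The rule therefore all but ensures that the analysis ignores the design.

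This is not a detail left to an analysis plan that is not shown. The article states a selection rule, and a plan that followed it would inherit the weakness.

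**Working it through.** **Inputs from the article.** 56 assessable patients per arm, response rates 70% and 40%, 90% power, significance level 0.05 (Sample size); primary end point is change in LVMI.

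**Assumptions, not in the documents.** Baseline and follow-up LVMI are normal with equal variance and correlation ρ, taken as 0.3, 0.5, 0.7 and 0.9. The treatment effect is 0.45 or 0.78 SD of change. The rule is applied to baseline LVMI alone, which is taken to pass the end-point check whenever it is flagged.

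**1. The plan's own figure.** Two-sided, pooled variance under the null: n = [1.960·√(2·0.55·0.45) + 1.282·√(0.21 + 0.24)]² / 0.30² = (1.379 + 0.860)² / 0.09 ≈ 55.7, so 56 per arm. This reproduces and is not in dispute.

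**2. What p < 0.05 can detect.** A continuous covariate is flagged only if its standardised difference exceeds 1.98·√(2/56) = 0.37. A binary covariate needs 1.96·√(2p(1−p)/56), which is about 17 percentage points at p = 0.3 and about 19 at p = 0.5. Anything smaller is left alone.

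**3. How often the model changes.** A variable not balanced by design is flagged in 5% of randomisations, so it is omitted in 95%. With k independent variables the chance of at least one flag is 1 − 0.95^k: 23% for 5, 40% for 10, 64% for 20.

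**4. Power.** The unadjusted t test on change has noncentrality 0.45·√(56/2) = 2.38, or power of about 66% at any ρ. ANCOVA multiplies the variance by (1 − ρ²)/(2 − 2ρ) = (1 + ρ)/2. At ρ = 0.5 this is 0.75, so the noncentrality is 2.38/√0.75 = 2.75 and power is about 78%. Simulation at 56 per arm agrees:

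| ρ | (1 + ρ)/2 | Power, article's rule | Power, baseline always in | Gap (points) |
|---|---|---|---|---|
| 0.3 | 0.65 | about 67% | about 83% | 16 |
| 0.5 | 0.75 | about 67% | about 78% | 11 |
| 0.7 | 0.85 | about 66% | about 72% | 6 |
| 0.9 | 0.95 | about 66% | about 67% | 1 |

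Reading the planned 70% against 40% as a shift of a normal variable gives 0.524 + 0.253 = 0.78 SD. At that effect the rule has 98% to 99% power and ANCOVA 99% to 100%, a loss of about 1 point or less.

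**5. Overall type I error.** Followed mechanically, the rule rejects a true null in 4.0% to 4.8% of trials over ρ = 0.3 to 0.9, so it is slightly conservative.

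**6. Error under moderate imbalance.** Take null trials whose baseline LVMI t statistic lies between 1.5 and 1.98 in absolute value (p from about 0.14 down to 0.05). They are 0.136 − 0.050, or about 9%, of all trials, and the rule leaves them unadjusted. The t test on change then rejects in about 12%, 11%, 8% and 6% for ρ = 0.3, 0.5, 0.7 and 0.9 (smaller runs put the first nearer 13%). ANCOVA stays at about 5%. Where the baseline statistic is 1.5 or less, the unadjusted test rejects in 3.2% to 4.7%, which is why the overall rate holds.

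**The case against.** A reader might take the point further than the article allows, in three ways.

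- **That the p-value loses its meaning or type I error is inflated.** It is not: the overall rate is about 4% to 5%. Even reporting the better of the adjusted and unadjusted models, with ten assumed covariates, gives only about 5.3% to 6.0%. The excess rejections in step 6 concern about 9% of null trials and fade as ρ rises.
- **That trial outcomes choose the model.** The Discussion places the end-point check alongside statistical considerations. It does not say whether the relationship is estimated from trial data or judged from prior knowledge. What stands is that the check comes after randomisation and has no stated criteria.
- **That the rule itself costs power.** The unadjusted test has about 66% power and the rule 66% to 67%. The gap comes mainly from the unadjusted default. The rule's fault is that it recovers almost none of it.

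There are also real mitigations. Stratification balances medication, sex and family history by design. A change score already subtracts baseline, so at high ρ little is lost. At an effect as large as the sample size suggests, the power difference nearly vanishes. These points limit the size of the problem. They do not give a reason to select covariates by baseline p-values.

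**Conclusion.** The concern holds as a weakness of the stated adjustment rule that should be corrected, not as a threat to validity. Two parts need no assumption about the outcome: an unstratified predictor such as baseline LVMI is omitted in about 95% of realisations, with standardised imbalances up to about 0.37 left uncorrected, and the covariate set is not fixed in advance.

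The power forgone against always adjusting for baseline LVMI runs from near 0 to about 16 points. It is largest at a moderate effect with low correlation, and about 1 point or less at 0.78 SD. That range rests on the assumed correlation and effect, neither of which the article gives.

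**What to change.** Delete the p < 0.05 trigger in the Discussion, the end-point check that follows it, and the conditional sentence under Analysis. In their place, state before unblinding that the primary LVMI analysis is an ANCOVA that always includes baseline LVMI and the stratification factors (ACEI, ARB or aldosterone antagonist use; sex; family history), whatever the observed balance. Present baseline characteristics by arm without p-values. Label any further adjustment as sensitivity analysis.

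The cost is wording only. Baseline echocardiography and the stratification factors are already collected, and no extra patients or visits are needed.
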